### Trial design

This study is a 2-arm cluster-RCT with a parallel group design, which compares the ACP-GP intervention (arm 1) to usual care (arm 2) of patients with a chronic life-limiting illness. It is a superiority trial which aims to establish whether the intervention is superior to usual care in its effectiveness. GPs, their patients, and the (potential) SDM of each patient will be recruited for participation. Randomization occurs at the level of the GP, with patients and their SDM clustered per GP. To determine effectiveness, outcomes will be measured at baseline (T0), during a first follow-up at 3 months (T1) and again at 6 months post-baseline (T2).

A process evaluation will be used to evaluate how the intervention was implemented and to understand which factors contributed to the results of the trial. This process evaluation follows the RE-AIM framework, which highlights essential factors to improving the adoption and implementation of evidence-based interventions: Reach, Efficacy, Adoption, Implementation, and Maintenance [20]. The process evaluation will span the duration of the intervention, as well as pre- and post-intervention evaluation.

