**Efficacy/effectiveness**	• Primary and secondary outcomes of the RCT	• See primary and secondary outcomes above • Reports of any adverse effects			
**Adoption**	• ACP discussion documents uploaded • Patient use of the work booklet • Experiences of GPs and patients applying intervention steps • Changes in GP practice	• Training topic checklist (after each training) • Questionnaire for GPs regarding their ACP practices and conversations in the last 3 months (T1) • Questionnaire for patients regarding ACP conversations with their GP in the last 3 months (T1) • Documentation template review (T1, T2) • Contents of work booklet from a sample of patients in the intervention group (physical copy or digital scan) (T1, T2) • Check-in discussions between GPs and trainers (continuous) • Focus groups with GPs (after T2) • Semi-structured interviews with patients and SDM (after T2)			
**Implementation**	• Fidelity: the extent to which the steps of the intervention were followed as specified in the protocol • Patient and GP barriers/facilitators to following the steps of the intervention • Satisfaction of GPs and patients with the intervention components	• Training topic checklist (after each training) • Check-in discussions between GP and trainers (continuous) • Audio recordings of ACP consultations between GP and patient (and SDM if present) • Documentation template review (T1, T2) • Satisfaction questionnaire for intervention GPs and patients (T1) • Focus groups with GPs (after T2) • Semi-structured interviews with patients and SDM (after T2)			
**Maintenance**	• GP intention for using the intervention materials in the future • Recommendations by the GP and patients to improve intervention usability in the future	• Satisfaction questionnaires for intervention GPs and patients (T1) • Focus groups with GPs (after T2) • Semi-structured interviews with patients and SDM (after T2)			

We have two separate primary outcomes, one at the GP level and one at the patient level. Success on any one of these outcomes at T1 may support a conclusion of effectiveness. Hence there are several ways for the study to successfully demonstrate a treatment effect. This multiplicity problem has been taken into account in the power analysis by controlling the Type I error rate at 2.5% (Bonferroni method).

Scores on the ACP Engagement Survey and the ACP Self-Efficacy Scale for GPs will also be measured at T2. We will treat T2 scores on these scales as a secondary outcome.

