### Sample size

All power calculations were conducted to allow testing for intervention effectiveness at T1. Power calculations were conducted for the primary outcome at the patient level and at the GP level.

When all clusters have the same size of 2 patients, and we assume an intracluster correlation coefficient (ICC) of 0.04 [32], then the design effect is estimated at 1.04, and a sample of 26 patients for each group (corresponding to 13 GPs with each 2 patients) will achieve 91.45% power to detect a mean difference in delta outcome of 1 at a significance level of 2.5%, assuming the standard deviation is 0.96 in both groups. This number has been increased to 51 patients per group (corresponding to 17 GPs with each 3 patients) to allow for an initial GP drop-out rate of 23.53% and a patient drop-out rate of 33.33%. (Total sample size of 102 patients).

A sample of 14 GPs for each group will achieve 91.11% power to detect a mean difference in ACP self-efficacy of 1 at a significance level of 2.5%, assuming the standard deviation is 0.71 in both groups. This number has been increased to 18 GPs per group to allow for an initial GP drop-out rate of 22.22% (Total sample size of 36 GPs).

To ensure sufficient statistical power for both GP- and patient-level primary outcomes, we will use the more conservative calculation of 18 GPs per group (36 total), with 54 patients per group (108 total) and a maximum of 54 SDMs per group (1 per patient, 108 total).

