##### Primary efficacy analyses

To test the effectiveness of the intervention, we will compare T1 scores on the ACP Engagement Survey for patients and the ACP-Self Efficacy Scale for GPs between the intervention and control arms. Linear mixed models will be used. For patient outcomes, the models will include a random intercept for GP (to account for the nesting of patients within a GP) and a random intercept for patient (to account for the nesting of repeated measurements within a patient). For GP outcomes, a random intercept for GP (to account for the nesting of repeated measurements within a GP) will be used. The fixed effects part of these linear mixed models will include time, group, and time x group interaction. The two-way interaction between time and group will capture the effect of the intervention.

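### The primary effect is named as an unqualified time-by-group interaction over three visits, so the T1 test is not pinned down, and the free baseline means cost precision

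*Protocol article*

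**What the plan says.** All references are to the protocol article.

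- **Primary efficacy analyses** opens by saying that "we will compare T1 scores on the ACP Engagement Survey for patients and the ACP-Self Efficacy Scale for GPs between the intervention and control arms". It specifies linear mixed models with random intercepts, and continues: "The fixed effects part of these linear mixed models will include time, group, and time x group interaction". It closes with "The two-way interaction between time and group will capture the effect of the intervention". The coding of time is not given, and no contrast within the interaction is named.
- **Trial design** sets three measurement times: baseline (T0), 3 months (T1) and 6 months (T2).
- **Study endpoints and assessments** defines success on either primary outcome at T1 and says of the same two scales: "We will treat T2 scores on these scales as a secondary outcome".
- **Sample size** states that all power calculations are for T1. The patient calculation is for a difference of 1 in the delta outcome with SD 0.96. The GP calculation is for a "mean difference in ACP self-efficacy of 1 at a significance level of 2.5%, assuming the standard deviation is 0.71 in both groups".
- **Blinding** says that T0 data are collected before randomisation.
- **Data analysis** sets each primary test at two-sided 2.5% and lets secondary endpoints be tested at 5% once a primary effect is shown.

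**The concern.** With three visits and two arms, a time-by-group interaction is not a single number. With categorical time it has two components, the arm difference in change to T1 and the arm difference in change to T2. The usual software test of the term is a joint 2-df test of both. With time as a linear covariate it is a difference in slopes. Only the first component, taken alone, matches the declared T1 endpoint. The closing sentence does not select it, so analysts could follow the section in good faith and reach different primary p-values. Because a primary success opens the secondary tests at 5%, the choice affects more than one result.

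A second matter remains when the T1 component is chosen. Including a group main effect means that the model estimates a T0 arm difference whose expected value is zero by design. The T1 interaction coefficient is then a plain difference in change scores, which uses the baseline less efficiently than a common-mean or baseline-adjusted model does. It may also differ from the quantity on which the GP sample size was based.

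**Working it through.** **Inputs from the protocol.** Two-sided alpha 0.025. Patients: 26 per arm, design effect 1.04, difference 1, SD 0.96, stated power 91.45%. GPs: 14 per arm, difference 1, SD 0.71, stated power 91.11%. Visits at 0, 3 and 6 months.

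**Assumptions.** The T0–T1 correlation (rho) is not given, so a range of 0.3 to 0.8 is shown. Variances at T0 and T1 are taken as equal, data as complete, and correlations over time as compound-symmetric, which is what the random intercepts imply.

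**1. Reproducing the stated power** (two-sample t test, noncentral t)
- Patients: effective n = 26/1.04 = 25 per arm, giving 91.1%.
- GPs: n = 14 per arm, giving 90.3%.

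Both are within a percentage point of the stated figures.

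**2. What each reading of the interaction tests** (patients, 0.96 read as the SD of change)
- *T1-by-group coefficient, categorical time.* This is the arm difference in T1 minus T0, which is the quantity in the patient power calculation. T2 does not enter when data are complete.
- *Joint 2-df test.* The covariance of the two change contrasts is 0.96² × (2/25) × [[1, 0.5], [0.5, 1]]. With no T1 effect, a T2 effect of 1 gives noncentrality 18.1 and rejection probability 94.6%. A T2 effect of 0.5 gives noncentrality 4.5 and 34.0%.
- *Linear slope.* For equally spaced visits the weights on T0, T1 and T2 are proportional to −1, 0 and +1, so T1 has no weight. An effect of 1 at T1 and 0 at T2 is detected with probability 2.5%, which is alpha. An effect of 0 at T1 and 1 at T2 is detected with probability about 92%.

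**3. Cost of free baseline means on the T1 reading**
- Change contrast: variance proportional to 2σ²(1−rho).
- Common T0 mean, or T1 adjusted for T0: variance proportional to σ²(1−rho²).
- Ratio: 2(1−rho)/[(1−rho)(1+rho)] = 2/(1+rho), which is 1.54 at rho 0.3, 1.33 at 0.5 and 1.11 at 0.8.

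If 0.96 is the SD of change, patient power stays at 91.1% with free means. With a common T0 mean it would be 98.6%, 97.2% and 93.8% at rho 0.3, 0.5 and 0.8.

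**4. GP power if 0.71 is a score SD** (14 per arm)

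The SD of change is 0.71 × √(2(1−rho)). The baseline-adjusted SD is 0.71 × √(1−rho²).

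| rho (assumed) | SD of change | Power, change | Adjusted SD | Power, constrained or adjusted |
|---|---|---|---|---|
| 0.3 | 0.840 | 77% | 0.677 | 93% |
| 0.4 | 0.778 | 84% | 0.651 | 95% |
| 0.5 | 0.710 | 90% | 0.615 | 97% |
| 0.6 | 0.635 | 96% | 0.568 | 98.6% |
| 0.7 | 0.550 | 99% | 0.507 | 99.7% |
| 0.8 | 0.449 | over 99.9% | 0.426 | over 99.9% |

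Break-even with the planned power is at rho 0.5, where the SD of change equals 0.71.

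**The case against.** The strongest reply is that the protocol fixes T1 repeatedly: in the first sentence of the primary analysis section, in the definition of success, in the sample size section, in the significance-level rule, and in the section on interim analyses. Read together, these make the T1-by-group coefficient the natural meaning, and time coding can be left to an analysis plan. This largely stands. A reader might infer that the primary test is a joint or slope test over T0 to T2, so that a T2-only effect would count as a primary success. The document nowhere says so, and the T2-only probabilities above hold only under readings that it does not select. What remains is that the protocol does name the parameter that carries the effect, and names it without restriction to T1. That is imprecise text rather than deferred detail.

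A reader might also infer that the trial is not powered for its planned test. For patients this fails, because the calculation is stated for the delta outcome, which on its plain reading is the change contrast. For GPs a shortfall needs both that 0.71 is a score SD, which the protocol does not say, and that rho is below 0.5. Above 0.5 the change contrast exceeds the planned power. If 0.71 is an SD of change, there is no shortfall at all. The 14 per arm also already allows for drop-out: with all 18 GPs per arm retained, power at rho 0.3 would be 88.4%.

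Finally, free baseline means give a valid, unbiased estimate in a randomised trial, so constraining them is a gain in precision and not the correction of an error. Nor does the joint test always lose power: for an effect of 1 at both visits it has 94.6%. Both points are accepted.

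**Conclusion.** The point holds as an ambiguity plus an avoidable loss of efficiency. The closing sentence of the primary analysis section should be tied to T1, because as written it leaves room for tests that a secondary time point could decide. The context makes the T1 coefficient the likely intention. On that reading the change contrast has 1.54 to 1.11 times the variance of a baseline-constrained contrast over assumed rho 0.3 to 0.8. The estimate is not biased, and the planned patient power is met if 0.96 is the SD of change. GP power is uncertain rather than shown to be deficient: it runs from about 77% to over 99.9% over the assumed range if 0.71 is a score SD, while the constrained or adjusted contrast stays at about 93% or more throughout. These figures assume complete data, equal variances and compound symmetry. The correlation is an assumption, as the protocol gives none.

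**What to change.** Replace the closing sentence of the primary analysis section with wording to this effect: time is categorical; for each primary outcome the test, at two-sided 2.5%, is the single-df between-arm contrast at T1 from a model with a common T0 mean in both arms, or from a model of T1 adjusted for T0; the T2 contrast is secondary. In the sample size section, state whether 0.71 is the SD of a score or of a change, and base the GP power statement on the chosen contrast with the assumed correlation given.

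This costs only wording in the protocol or analysis plan. It needs no extra participants, visits or data. It should be settled before any unblinded analysis, since it determines the primary p-values.

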##### Secondary efficacy analyses

All continuous secondary endpoints will be analyzed by fitting similar linear mixed models as described above. Binary, multinomial, ordinal and count endpoints will be analyzed by fitting Generalizing Estimating Equations (GEE) models using a compound symmetry (or exchangeable) correlation structure, where we assume all correlations between time points to be the same. The GEE approach is a robust approach to take into account the repeated measurements within GPs without distributional assumptions. It is robust against misspecification of the covariance structure. However, it only allows missing values to be missing completely at random. Only an independent correlation structure is available for multinomial GEE models in SAS and SPPS software. Therefore, for nominal endpoints with K response categories, we will fit K-1 separate binary logistic GEE models for each response category paired with a baseline category.

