#### Data analysis

The intent-to-treat population consists of all patients randomized. Subjects are analyzed according to the allocated treatment group irrespective of their compliance with the planned course of treatment. The intent-to-treat population is considered the main analysis population.

Linear mixed models will give unbiased results when outcome data is missing at random (maximum likelihood estimation). GEE models only allow for missing values to be completely at random (it is not a likelihood approach).

The analyses of the two separate primary endpoints will be performed at the two-sided 2.5% significance level, because success on any one of these endpoints at T1 may support a conclusion of effectiveness (Bonferroni method to adjust for multiplicity).

When an effect on a primary endpoint is shown, the secondary endpoints can be analyzed at the two-sided 5% significance level.

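### The GEE robustness claim omits its large-sample condition: with 26 to 36 GP clusters, the usual sandwich variance would make tests of common patient-level binary secondary endpoints run at about 6–7% instead of 5%

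*Protocol article*

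**What the plan says.** Under Secondary efficacy analyses the article states: "Binary, multinomial, ordinal and count endpoints will be analyzed by fitting Generalizing Estimating Equations (GEE) models using a compound symmetry (or exchangeable) correlation structure". It gives the reason in two sentences: "The GEE approach is a robust approach to take into account the repeated measurements within GPs without distributional assumptions", and then "It is robust against misspecification of the covariance structure". The only limit it attaches to GEE is that missing data must be missing completely at random. It names no variance estimator, small-sample correction or reference distribution.

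Under Sample size, 18 GPs per group are recruited with three patients each: 36 GPs and 108 patients. The GP calculation needs 14 per group after drop-out: "A sample of 14 GPs for each group will achieve 91.11% power to detect a mean difference in ACP self-efficacy of 1". The patient calculation rests on 13 GPs per group with two patients each.

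Under Data analysis, once a primary endpoint shows an effect, "the secondary endpoints can be analyzed at the two-sided 5% significance level". The Objectives list these outcomes as ones to explore.

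**The concern.** The sandwich variance is consistent under a wrong working correlation as the number of independent clusters grows. With few clusters it is biased downwards, and its own sampling variation calls for a t reference rather than a normal one. Both effects make intervals too narrow.

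The robustness sentence carries real weight here. With GP as the cluster, a single exchangeable correlation treats two measurements on one patient like measurements on two different patients of the same GP. For patient-level outcomes that structure is almost certainly wrong, so valid inference depends on the sandwich.

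At stake is the error rate and interval coverage for common binary patient endpoints. Appointment of an SDM is the clearest example: Table 3 has it measured at T0, T1 and T2.

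**Working it through.** **1. Number of clusters, from the plan's own figures.**
- Randomised: 2 × 18 = 36 GPs.
- GP calculation: 1 − 14/18 = 22.22% drop-out, as stated, leaving 28 GPs. With a difference of 1, SD 0.71, 14 per group and two-sided 2.5%, power is 90.3% (noncentral t) or 93.1% (normal), against the stated 91.11%.
- Patient calculation: 1 − 13/17 = 23.53%, as stated, leaving 26 GPs. The effective sample is 26/1.04 = 25 per group. With a difference of 1 and SD 0.96, power is 91.1% (t) or 92.5% (normal), against the stated 91.45%.
- The t versions agree with the stated power to within one point, so 26, 28 and 36 are the relevant cluster counts. The 26 comes from a 17-GP design; 36 × 13/17 = 27.5 GPs would remain from the 36 actually recruited.

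**2. Closed form for a symmetric outcome.** With n GPs per arm, the uncorrected sandwich divides by n where n − 1 is unbiased. The size of a nominal 5% z-test is then P(|t with 2n − 2 df| > 1.96 × √((n − 1)/n)).

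| GPs per arm | df | Size | Of which from z in place of t alone | Widening of a corrected 95% interval |
|---|---|---|---|---|
| 18 | 34 | 6.5% | 5.8% | 7% |
| 14 | 26 | 7.0% | 6.1% | 9% |
| 13 | 24 | 7.2% | 6.2% | 10% |

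The widening is t(0.975, 2n − 2) × √(n/(n − 1)) / 1.96. For n = 14: 2.056 × 1.038 / 1.96 = 1.09.

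**3. Simulation under the null.** Logistic GEE, exchangeable correlation, GP as cluster, terms for time, group and their interaction; 4,000 trials per setting. Assumed, because the article gives no values: prevalence 0.3 or 0.5; for patient outcomes, latent variance shares of 0.08 (GP) and 0.30 (patient); for GP outcomes, a within-GP share of 0.30. Simulation error is about 0.4 points. The contrast is group by time, which the article names as the intervention effect for the linear mixed models; I assume the same for GEE.

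| Setting | Uncorrected sandwich with z |
|---|---|
| Patient outcome, 36 GPs × 3 | 6.2–7.0% |
| Patient outcome, 28 GPs × 3 | 6.8–6.9% |
| Patient outcome, 28 GPs × 2 | 6.2–6.4% |
| Patient outcome, 26 GPs × 2 | 6.5% |
| GP outcome, three time points, 36 GPs | 5.4–5.9% |
| GP outcome, three time points, 28 GPs | 4.6–6.5% |
| Patient outcome, single time point, 36 × 3 | 5.1% |
| Patient outcome, single time point, 28 × 2 | 5.7% |
| Control: 200 clusters × 3 (1,000 trials) | 5.5% |

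For the patient outcomes with two time points, the empirical SD exceeded the mean reported standard error by 4% (0.485/0.465, 36 × 3) to 8% (0.820/0.762, 26 × 2).

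**4. Variation of the assumptions.** With an independence working correlation, each follow-up kept with probability 2/3, and prevalence 0.2–0.5, the size was 5.7–6.3% (18 per arm), 6.2–6.6% (14) and 6.5–7.1% (13), with the SD 3–8% above the standard error.

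**5. Corrected inference.** For patient-level binary group-by-time contrasts at prevalence 0.2–0.5, a further simulation gave 6.1–6.8% uncorrected and 4.1–4.8% with Kauermann-Carroll and t (GPs − 2). Mancl-DeRouen with the same t gave 2.2–4.8% over the settings in step 3.

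**The case against.** The strongest reply is that the article never says the variance is uncorrected. It is a condensed article, its analysis plan is not shown, and a bias correction is the kind of detail left to that plan. This stands. A reader might infer that the trial has chosen the wrong variance, and the text does not support that. What remains is a sentence that is present and too broad: the article discusses limits of GEE, down to what software offers for multinomial models, yet states robustness without the condition that matters at this size.

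A second reply is that the inflation is not general, and this also stands. A reader might infer that every non-continuous endpoint exceeds 5%.
- Completion of new ACP documents has no T0 measurement in Table 3, so a baseline-to-T1 contrast does not exist for it. T1-only contrasts ran at about 4.5–6.2% for prevalence 0.2–0.5.
- At prevalence 0.1 the T1-only size was 1.1% (14 GPs per arm) and 1.8% (18 per arm), well below nominal.
- GP-level results straddle 5%.
- Ordinal models were not examined, and no claim is made for counts.

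A reader might also expect patient drop-out to worsen the error. In the T1-only setting with 14 GPs per arm it lowered it: 4.6%, 5.8% and 6.2% with one-third drop-out, against 5.9%, 6.2% and 6.7% without, at prevalence 0.2, 0.3 and 0.5.

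Third, the Recruitment section replaces GPs who leave in the first three months, so the count at T1 should be nearer 36 than 26. This is fair, but the excess for patient-level group-by-time contrasts persists at 36 GPs (5.7–7.0% across the simulations).

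Finally, the endpoints are exploratory and tested only after a primary effect. That limits the consequence; it does not make the stated 5% level accurate.

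**Conclusion.** The point holds in a limited form. The article rests the GEE analyses on a large-sample property with 36 GP clusters, or 26 to 28 under its own drop-out allowance. If the method is run as described with the usual sandwich and a normal reference, the true SD is about 3–8% above the reported standard error for common patient-level binary endpoints. The nominal 5% test of the group-by-time contrast then has a size of about 6–7%. This depends on assumed prevalences of 0.2–0.5 and assumed correlations. The direction is supported by the closed form, and the near-nominal 200-cluster control is consistent with a small-cluster effect. The primary outcomes and the trial's main conclusion are not affected. Minor, with moderate confidence in the exact size.

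**What to change.** Qualify the robustness sentence under Secondary efficacy analyses by noting that it depends on a large number of clusters. Then add one sentence: GEE inference takes the GP as the cluster for both GP-level and patient-level outcomes, uses a Kauermann-Carroll bias-corrected variance, and bases tests and intervals on a t distribution with number of GPs minus 2 degrees of freedom. Mancl-DeRouen with the same t reference is an alternative but more conservative. If the analysis plan already specifies such a correction, a cross-reference is enough.

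The cost is one sentence, standard software, and intervals wider by roughly 7–10% in the symmetric case. Sparse or GP-level binary outcomes, some of which are already at or below 5%, will be tested somewhat conservatively. Fixing the choice in advance also removes a later choice between variance estimators that could decide a borderline result.
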